The allocation ratio of randomisation is 1:1. The randomisation sequence will be generated using a computer-generated block randomisation (StataCorp 2017. Stata Statistical Software: Release 15) using blocks of sizes 2, 4 and 6 over 144 participants per stratum (stratified by research centre). Opaque envelopes will be prepared in advance, numbered sequentially by alternating between stratums by block. After conducting the baseline assessment, the clinical midwife/nurse will open the envelope and announce the cognitive task to be carried out (ie, the cognitive visuospatial task or the attention-placebo control task) to the participant.^95^ All members of the research group as well as participants are blind to group allocation. All participant data will be coded to ensure confidentiality. After completing the 15 min cognitive tasks, both women of the control and intervention group will complete the same assessments, as shown in table 1; see figure 1 for an overview of the study variables.

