### Sample size calculation

Based on a previous proof-of-principle RCT,^4^ a sample size of n=120 participants is necessary to have 80% power (α=0.05) to detect a between-group difference of d=0.30 of the primary outcome (PTSD symptoms at 6 weeks). Furthermore, we calculated the sample sizes necessary to obtain significant group differences with 80% power (α=0.05) based on small effect sizes (d<0.30) for maternal secondary outcomes (PTSD diagnosis, ASD symptoms and physiological stress reactivity) and infant secondary outcomes (physiological stress reactivity) based on small effect sizes (d<0.30) with 80% power (α=0.05), which range between a total of n=56 and n=84. Predicting a 20% drop-out rate, we aim to recruit 144 women.

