## Data management and statistical analyses

All study data will be entered by research staff. Study data will be managed using Research Electronic Data Capture (REDCap) tools hosted at Lausanne University Hospital.^131 132^ REDCap is a secure, web-based software platform designed to support data capture for research studies. Double data entry will be done for the primary outcomes. For the rest of the data, a random 5% will be double checked. Access to the full final trial dataset will be restricted to the principal investigator.

For the primary analyses, group differences regarding the mean subscale and total scores of the PCL-5 and CAPS-5 at 6 weeks will be analysed using separate linear regression analyses. Analyses will be adjusted for recruitment centre and the respective baseline values. Associations between primary outcomes and potential confounders, such as maternal and gestational age, will first be assessed applying univariate tests. Subsequent analyses will be adjusted for significant covariates. For secondary aims, the analyses will be performed for differences in changes between groups and differences between groups at different time points in maternal and infant outcomes. Proportion of participants meeting the diagnostic criteria for PTSD at 6 weeks and 6 months between the two groups will also be compared using logistic regression analyses. The same procedure for identifying significant covariates described above will be applied here. Furthermore, post hoc exploratory analyses will be conducted but described as such in publications. All regression analyses regarding cortisol data will be adjusted for potential covariates, such as cosleeping, breastfeeding, menstrual cycle, and infant and maternal medication. For HRV analyses, interbeat intervals from baseline, stress task and recovery will be analysed by the extraction from ECG recordings. Statistical parameters of HRV^133^ will be calculated using Kubios HRV Analysis V.2.2 software.^134^ Time domain measures and spectral frequency measures will be used for calculations. Multiple imputation methods will be used to manage missing data, if appropriate.

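### Additional covariates in the primary and PTSD-diagnosis models are picked by univariate significance tests on the trial's own outcome data, from an open candidate list, instead of being fixed in advance

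*Protocol article*

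**What the plan says.** The primary analysis is a set of separate models: "group differences regarding the mean subscale and total scores of the PCL-5 and CAPS-5 at 6 weeks will be analysed using separate linear regression analyses". Some adjustment is fixed: "Analyses will be adjusted for recruitment centre and the respective baseline values".

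A selection step follows in the same paragraph: "Associations between primary outcomes and potential confounders, such as maternal and gestational age, will first be assessed applying univariate tests", and then "Subsequent analyses will be adjusted for significant covariates". For the logistic regressions of PTSD diagnosis at 6 weeks and 6 months, the article adds: "The same procedure for identifying significant covariates described above will be applied here".

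Only two candidates are named, as examples: "potential confounders, such as maternal and gestational age". The article gives no significance threshold, does not restrict candidates to values that precede randomisation, and does not say whether one set serves all models or each model gets its own.

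The section on study population, recruitment, allocation and blinding states "The allocation ratio of randomisation is 1:1", with stratification by centre.

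**The concern.** Screening covariates against the outcome is a habit from observational work, where confounding is the worry. In a randomised comparison, baseline imbalance is due to chance. A covariate earns its place by explaining outcome variance, and that can be judged before the data exist.

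Four things are at stake.

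- The covariate part of the primary model is chosen after looking at the outcome.
- A truly prognostic variable can miss the cut-off by chance and be left out.
- The covariate sets may differ between the CAPS-5 and PCL-5 models, which would make their adjusted effects harder to compare.
- An open list leaves room for choice by the analyst, and does not keep out variables that arise after the task. Table 1 schedules social support and sleep measures only from the first week onward. If such a variable were affected by treatment, adjusting for it would bias the effect estimate.

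**Working it through.** The plan attaches no figure to this rule, so there is none to reproduce. The check asks what the rule does at about the planned number of completers.

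**Inputs from the article.** Recruitment of 144 with 20% drop-out gives 144 × 0.80 = 115.2 women; 116 (58 per arm) was used in simulation. Allocation is 1:1, and centre is a fixed covariate.

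**Assumed inputs.** Screening threshold p<0.05, 2 to 20 independent candidates, and the prognostic strengths shown below.

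**1. Noise entering the model.** If none of k candidates is prognostic, the chance that at least one enters is 1 − 0.95^k:

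| k | chance |
|---|---|
| 2 | 10% |
| 5 | 23% |
| 10 | 40% |
| 20 | 64% |

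**2. Prognostic variables dropped.** By Fisher's z, a predictor with correlation r passes with probability Φ(atanh(r) × √(116 − 3) − 1.96).

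- r = 0.25: Φ(0.2554 × 10.63 − 1.96) = Φ(0.755) = 0.775. At least one of three is lost with probability 1 − 0.775³ = 53%; one of four, 1 − 0.775⁴ = 64%.
- r = 0.30: Φ(0.3095 × 10.63 − 1.96) = Φ(1.33) = 0.908. At least one of three is lost with probability 1 − 0.908³ = 25%.

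Simulation gave 25% to 66% over such cases.

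**3. Type I error.** Null treatment effect, 10,000 replicates per scenario, 2 to 20 candidates:

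- screened model: 4.5% to 5.4% (a second simulation gave 4.5% to 5.5%);
- all candidates fixed in advance: 4.4% to 5.2%;
- significance verdict differs between the centre-only and the screened model: 0.2% to 4.7% of trials;
- the more favourable of those two reported: 5.1% to 7.5%.

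**4. Power.** This was simulated at d = 0.5, not at the article's d = 0.30 ("a sample size of n=120 participants is necessary to have 80% power (α=0.05) to detect a between-group difference of d=0.30"). With 60 per arm, two-sided 80% power is reached at d = (1.96 + 0.84) × √(2/60) = 0.51. Whether n=120 suits d = 0.30 is a separate question.

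| assumed predictors | screened | fixed set holding the true predictors | loss |
|---|---|---|---|
| two, r = 0.40 | 0.886 | 0.900 | 1.4 points |
| three, r = 0.25 | 0.815 | 0.842 | 2.7 points |

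**5. Events for the diagnosis model.** The introduction gives postnatal PTSD rates of 19% to 39% after obstetric complications such as ECS. That is 115 × 0.19 = 22 to 115 × 0.39 = 45 events. A model with five terms (group, centre as one parameter, a symptom score, two ages) has 22/5 = 4.4 to 45/5 = 9 events per term. Without the symptom score it has 22/4 = 5.5 to 45/4 = 11. The covariate set for these models must therefore be small.

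**The case against.** **A condensed article may leave the list and threshold to the full protocol or SAP.** This stands for the list and threshold. It does not cover the rule: selection by outcome significance is stated as the method, and a SAP that merely closed the list would still carry it out.

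**The measured harm is small.** This stands. A reader might infer an inflated false-positive rate; the simulations do not show one for the rule as stated. A rate near 10% appears only if an analyst may report the best of seven versions, which is selective reporting and not what the article plans. Screening also did better than no covariate adjustment (power 0.79 against 0.75, and 0.88 against 0.76, at d = 0.5). Its 1-to-3-point loss is measured against a fixed set that happens to hold the right variables.

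**Different sets per outcome are not stated.** This stands. A reader might infer that CAPS-5 and PCL-5 will carry different covariates, but one pooled set fits the wording equally well. If screening were run per outcome, sets would differ in 67% to 84% of trials with 20 candidates, but in 11% to 15% with two non-prognostic candidates and 26% to 32% with five. The article names two.

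**Post-task covariates are not proposed for the primary models.** Both named examples are settled before randomisation, and many items recorded in the first week describe earlier facts. The gap is only that nothing rules out post-task variables. The same paragraph does accept breastfeeding and cosleeping as covariates for the cortisol models.

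**Centre and baseline adjustment are prespecified.** This stands, so it would be too broad to call the whole primary result data-driven. However, Table 1 schedules CAPS-5 and PCL-5 only at 6 weeks and 6 months. Centre is therefore the only fixed covariate certain to be available.

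**The wording on subsequent analyses could mean later sensitivity models.** This is possible, but the sentence sits in the primary-analysis paragraph, directly after a step said to come first. The primary models are the natural reading.

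**Conclusion.** The point holds in a limited form. The additional covariates for the primary and diagnosis models are chosen by significance in the trial's own outcome data, from an open list. Randomisation leaves no systematic confounding for that screen to remove.

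Applied mechanically to a closed list, the rule keeps type I error near 5% and costs about 1 to 3 points of power against a well-chosen fixed set. These sizes rest on the assumed number and strength of candidates, a 0.05 screen, about 116 women and, for power, d = 0.5. The cost lies mainly in an outcome-dependent model, prognostic variables lost by chance (25% to 66% of trials under the moderate strengths assumed) and avoidable freedom in the analysis. The text does not support claims of inflated type I error, of CAPS-5 and PCL-5 models certain to differ, or of planned adjustment for post-task variables. This is a worthwhile correction of wording, not a threat to the trial's validity.

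**What to change.** Delete the univariate screening step. Before any outcome data are seen, name one short closed set of pre-randomisation covariates for all primary models: centre, maternal age and gestational age.

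Add a T1 symptom score only if it is confirmed to be completed before the envelope is opened. The article does not settle this. The allocation section puts a baseline assessment before the envelope, but the maternal outcomes section places acute stress symptoms at 6 hours or later after the ECS. The T1 column of Table 1 also holds the feedback form completed after the task.

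Use the same set for the diagnosis models, or a smaller one given 22 to 45 expected events. Report the group-plus-centre model, and any screened model, as labelled sensitivity analyses.

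The change needs no new data and no change in sample size. Its downside is that the team must commit now to a few covariates, which may not turn out to be the most prognostic.

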## Introduction

### Childbirth and post-traumatic stress disorder

Though childbirth is a common and often fulfilling event, one-third of mothers rate their childbirth as traumatic.^1^ Childbirth can meet diagnostic criteria for a traumatic event, if women perceived their life and/or the life of their baby to be in danger.^2^ Post-traumatic stress disorder (PTSD) related to childbirth is diagnosable in around 3%–4% of women.^3 4^ According to the Diagnostic and Statistical Manual of Mental Disorders, Fifth Edition (DSM-5), PTSD consists of four symptom clusters (intrusions, avoidance, hyperarousal and negative cognitions and mood) and can be diagnosed at least 1 month after the traumatic stressor occurred.^2^ Comparing different modes of childbirth, obstetric complications, such as emergency caesarean section (ECS), produce higher rates of postnatal PTSD (19%–39%).^3^ ECS is a relatively frequent event, and there is thus a need to better identify and support women who are vulnerable to developing PTSD following an ECS.

Postnatal PTSD can significantly influence the experience of subsequent pregnancies, with increased risk of maternal stress and its associated risks of intrauterine growth retardation, premature birth and low birth weight.^5–7^ It can lead to a fear of subsequent pregnancy and childbirth, sexual problems and avoidance of medical care.^8 9^ Postnatal PTSD can also have important negative consequences for breastfeeding, the attachment relationship with the baby and mother–infant interactions, with a subsequent detrimental impact on the development of the child, as well as for the couple relationship.^7 10–13^ PTSD is also highly comorbid with depression, for which there is substantial evidence of long-term negative effects on child development and behaviour.^14–16^ Estimated economic costs of perinatal mental health problems are about £8.1 billion for each 1 year cohort of UK births, of which 72% relate to adverse impacts on the child rather than the mother.^17^ In Switzerland, 16.7% of women in the perinatal period used mental health services.^18^ New and innovative evidence-based interventions are, therefore, needed to reduce those costs by preventing the development of postnatal PTSD.^19^

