**Figure 1 F1:**
[figure not shown]
Study variables: processes in mothers, partners, infants and their interactions following traumatic childbirth. ANS, autonomic nervous system; HPA, hypothalamic–pituitary–adrenal.

**Table 1 T1:** Overview of primary, secondary and other outcomes, measures and time points

	Domain	Variables	Instruments	Timing			
				6 hours after ECS (T1)	≤1 week (T2)	6 weeks (T3)	6 months (T4)
**Mother**	Sociodemographic and medical data	Sociodemographic variables	Demographic questionnaire		**X**	**X**	**X**
		Medical data	Obstetric data and pregnancy outcomes from medical records		**X**		**X**
			Menstrual cycle (if applicable)				**X**
			Breastfeeding diary/questions		**X**	**X**	**X**
	Acceptability and expectancy of the intervention	Satisfaction and expectancy	Feedback questionnaire	**X**			
	Maternal psychological vulnerability	Intrusive trauma-related memories	Trauma-related intrusive memories diary^4^		**X**		
		Stress exposure and perception	Post-Delivery Perceived Stress Inventory (PDPSI)^135^		**X**		
			Major life events^136 137^		**X**		**X**
			Postnatal Perceived Stress Inventory (PPSI)^138^				**X**
			Parenting Stress Index-Short Form (PSI-SF)^139 140^				**X**
		PTSD	Clinician-Administered PTSD Scale for DSM-5 (CAPS-5)^100 101^			**X**	**X**
			PTSD Checklist for DSM-5 (PCL-5)^102^			**X**	**X**
		ASD	Acute Stress Disorder Scale (ASDS)^106^	**X**	**X**		
		Anxiety	Hospital Anxiety and Depression Scale: anxiety subscale (HADS)^108^	**X**	**X**	**X**	**X**
		Depression	Edinburgh Postnatal Depression Scale (EPDS)^110^	**X**	**X**	**X**	**X**
		Social support	Modified Medical Outcomes Study Social Support Survey (MOS-8)^141^		**X**	**X**	**X**
			Revised Dyadic Adjustment Scale (RDAS)^142 143^		**X**	**X**	**X**
		Sleep	Pittsburgh Sleep Quality Index (PSQI)^113^		**X**	**X**	**X**
			Pittsburgh Sleep Quality Index Addendum for PTSD (PSQI-A)^115^		**X**	**X**
			Morningness-Eveningness Questionnaire (MEQ)^144^		**X**
			Sleep diary		**X**		
			Overnight accelerometer assessments (GENEActiv®)^145^		**X**		**X**
	Maternal physiological stress responses	Physiological regulation	Baseline cortisol and cortisol daily profile (saliva)		**X**		**X**
			Resting heart rate and heart rate variability (Firstbeat Bodyguard 2)				**X**
		Physiological stress reactivity	Cortisol (saliva)				**X**
			Heart rate variability (Firstbeat Bodyguard 2)				**X**

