### Intervention group

Mothers in the intervention group will be instructed to engage in a cognitive visuospatial task, the computer game Tetris, for 15 min continuously, on a handheld gaming device (Nintendo DS) (see ref. 4). They are given a 3 min training in how to play the game and how to actively use mental rotation as they play the game. The intervention is delivered in the same context as that in which the trauma occurred (eg, wake-up room) so additional memory reminder cue to the trauma is not used.

The intervention will take place within the first 6 hours after ECS while participants are still in their hospital bed. Procedures are managed not to interfere with important routine care procedures. An unblinded independent researcher will check during the days following the intervention that the intervention protocol was followed correctly via a four-item survey completed by the participant. Study information and materials refer to ‘simple tasks’ in both conditions for credibility.

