Partner-infant interaction	Mother-to-Infant-Bonding Scale (MIBS)^122^ (at ≤1 and 6 weeks, and 6 months follow-up)	Adapted for partners, **s**ee Measures section for more details
Demographic Information	Partner demographics (at ≤1 and 6 weeks, and 6 months follow-up)	Adapted for partners, **s**ee Measures section for more details
	Infant demographics (at ≤1 and 6 weeks, and 6 months follow-up)	**Mothers** report on their child’s weight and height.
Medical data	Breastfeeding diary and questions (at ≤1 and 6 weeks, and 6 months follow-up)	**Mothers** report on breastfeeding in a 2-day daily diary including breastfeeding length and type (exclusive or mixed).
Acceptability and expectancy of the activity	Self-report questionnaire of satisfaction and acceptability of the intervention (at ≥6 hours following ECS)	On completing the activity, **mothers** complete 7 items to assess intervention fidelity, satisfaction and acceptability of the intervention.
			Infant neurodevelopmental vulnerability	Dubowitz neurological examination^146^ (at ≤1-week follow-up)	Examination of the **infant** on 34 items subdivided into 6 categories (tone, tone patterns, reflexes, movements, abnormal signs and behaviour). Full examination by a paediatrician follows standardised instructions and takes 10–15 min.

Participant groups for whom the outcome is relevant are highlighted in BOLD.

ECS, emergency caesarean section.

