#### Maternal and infant physiological stress responses

Physiological regulation: Resting heart rate of the mother and infant are assessed using resting HRV measured by Firstbeat Bodyguard 2 devices providing a continuous measure of cardiac activity. Resting heart rate will be assessed during the 15 min resting period before the stress paradigms (see Physiological stress reactivity for stress paradigms) at ≤1 week and 6 months. Baseline salivary cortisol and cortisol daily profile will be established for the mother in the 2 days after leaving the maternity ward (usually the 6th and 7th day post partum) and for her and her baby for 2 days at 6 months through salivary sample; five saliva samples are taken per day, including CAR. Maternal salivary cortisol will be collected using Salivette Sarstedt (item number: 51.1534.500) and SalivaBio Infant’s Swab (Salimetrics, item number: 5001.08 50) for infants.

Physiological stress reactivity: Maternal and infant stress reactivity will be assessed via salivary cortisol and HRV using Firstbeat Bodyguard 2 devices during the stress phases of their respective stress paradigms at 6 months for the mother and at ≤1 week and at 6 months for the infant. The stress paradigm for the mothers is the Trier Social Stress Test^116^ at 6 months. Maternal salivary cortisol will be measured seven times before, during and after the stress paradigms and heart rate throughout the stress paradigm. Stress paradigms for the infants involve the Neonatal Behavioural Assessment Scale^117^ at ≤1 week and the double-exposure Face-to-Face Still-Face paradigm (FFSF)^118–121^ at 6 months. Salivary cortisol will be measured three times, once before and twice after the stressor, and HRV will be measured throughout the stress paradigms. Maternal cortisol will also be collected during the FFSF. Maternal salivary cortisol will be collected using Salivettes Sarstedt and SalivaBio Infant’s Swab for infants. Participation in physiological assessments at ≤1 week is optional (involving an additional consent obtained before hospital discharge).

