#### Sociodemographic, obstetric and neonatal characteristics

Mothers will report demographic information, including marital status, nationality, profession, level of education^129^ and previous and current psychiatric disease as well as any trauma history via a self-report questionnaire. Mothers will also report their height, weight (before pregnancy and current), menstrual cycle, smoking behaviours and alcohol/drug use. Obstetric data will be extracted from the hospital medical record, such as pregnancy-related, labour-related and birth-related information, gravidity, parity, mode of previous childbirths, history of miscarriage, stillbirth and prematurity, pain, medication, birth control, sexual activity and psychological support. Neonatal characteristics will be collected from the medical record on severity of morbidity (gestational age and weight at birth, Apgar score, neonatal complications), as well as the Clinical Risk Index for Babies,^130^ which represents neonatal morbidity severity.

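### The cortisol rule adjusts the between-group comparison for breastfeeding and other factors that arise after randomisation, which can bias the estimated total effect of the intervention

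*Protocol article*

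**What the plan says.** The rule is in Data management and statistical analyses: "All regression analyses regarding cortisol data will be adjusted for potential covariates, such as cosleeping, breastfeeding, menstrual cycle, and infant and maternal medication". It covers every cortisol regression, does not limit the covariates to values fixed before randomisation, and is not accompanied by any cortisol model without them.

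On timing, the section on recruitment and allocation says: "After conducting the baseline assessment, the clinical midwife/nurse will open the envelope and announce the cognitive task to be carried out". The Intervention group section adds: "The intervention will take place within the first 6 hours after ECS while participants are still in their hospital bed". Table 2 gives the breastfeeding record as "Breastfeeding diary and questions (at ≤1 and 6 weeks, and 6 months follow-up", and Table 1 agrees. The Table 1 row "Menstrual cycle (if applicable" is marked at 6 months only. Medication appears in the list of data from the hospital record ("history of miscarriage, stillbirth and prematurity, pain, medication, birth control, sexual activity and psychological support") with no time point. Cosleeping has no row in Table 1 or Table 2.

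The first maternal cortisol profile is collected "for the mother in the 2 days after leaving the maternity ward (usually the 6th and 7th day post partum". Other maternal and infant samples are at 1 week or earlier, or at 6 months. The Introduction states: "Postnatal PTSD can also have important negative consequences for breastfeeding".

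**The concern.** Randomisation makes the arms comparable at the moment the envelope is opened. A covariate fixed before that moment can be added to the model without harm. A covariate that develops afterwards may itself be changed by the allocated task, and conditioning on it does two things. It removes the part of the effect that runs through the covariate. It also makes the arms non-comparable on any unmeasured factor that influences both the covariate and cortisol.

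Physiological stress in mother and infant is a named secondary outcome, and the Sample size calculation section expects small effects for stress reactivity (d below 0.30). A modest bias would matter against effects of that size. The rule is also written as a commitment, so it is more than a detail left open for the analysis plan.

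**Working it through.** The plan states no figure on this point, so there is none to reproduce. The check has two parts: the timing and causal status of each covariate, and an illustration of the possible size.

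**Timing and path, covariate by covariate**

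| Covariate | Recorded or arising | Path from the intervention stated in the protocol? |
|---|---|---|
| Breastfeeding | Up to 1 week, 6 weeks, 6 months: after randomisation | Yes, through PTSD (Introduction) |
| Menstrual cycle | 6 months: after randomisation | No; plausible only |
| Cosleeping | No listed time point; can only begin after the birth | No; plausible only |
| Maternal and infant medication | Timing not given; some maternal medication may be peripartum | No |

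All cortisol is sampled after randomisation, so no pre-randomisation cortisol value exists to adjust for instead. The stated path through PTSD applies most directly to the 6-month samples. The Introduction says PTSD can be diagnosed only from 1 month after the event, and the first maternal profile is at about days 6 and 7. A path through early symptoms is possible but not stated.

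**Size, one mediator, no unmeasured common cause**

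Absolute bias is approximately (arm difference in the covariate caused by the intervention) × (its association with cortisol in SD). Both inputs are assumptions; the documents give neither.

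- No arm difference: 0 × any association = 0 SD.
- 10 points and 0.3 SD: 0.10 × 0.3 = 0.03 SD.
- 20 points and 0.5 SD: 0.20 × 0.5 = 0.10 SD.

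A 10 to 20 point difference is large if PTSD is the only route. The Introduction gives PTSD rates of 19% to 39% after emergency caesarean. Assume that the intervention halves these (a reduction of about 10 to 20 points) and that PTSD lowers breastfeeding by 20 to 30 points:

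- Low end: 0.10 × 0.20 = 0.02, a 2 point arm difference; × 0.3 = 0.006 SD.
- High end: 0.20 × 0.30 = 0.06, a 6 point arm difference; × 0.5 = 0.03 SD.

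Effects through symptoms below the diagnostic threshold could add to this.

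**Simulation**

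Cortisol was regressed on arm with and without the covariate in 2,000,000 simulated women allocated 1:1. All inputs are assumed: 60% breastfeeding in controls, a breastfeeding effect on cortisol of −0.5 SD, a direct effect of 0 or −0.2 SD, and an unmeasured common cause either absent or with loading 0.5.

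| Arm difference in breastfeeding | Bias, no common cause | Bias, with common cause |
|---|---|---|
| 0 points | 0.00 SD | 0.00 SD |
| 5 points | +0.03 SD | +0.04 SD |
| 10 points | +0.05 SD | +0.09 SD |
| 20 points | +0.10 SD | +0.18 SD |

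At 10 points with a direct effect of −0.2 SD, the true total effect is −0.2 + (−0.5 × 0.10) = −0.25 SD. The model without breastfeeding gives −0.25 SD. The adjusted model gives −0.20 SD, or −0.16 SD with the common cause. The sign of the bias follows from the assumed signs. In every scenario the model without the covariate returned the true total effect within simulation error.

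**The case against.** The strongest defence is that these are plausible sources of cortisol variation, that adjusting for them may tighten the estimates, and that the rule may be aimed partly at regressions of association between maternal and infant cortisol, where such adjustment can be appropriate. The list is also illustrative, and a condensed article need not set out every model. The precision argument stands as a reason to keep the adjusted model. It does not justify imposing that model on the randomised comparison, which the wording includes.

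Three stronger readings are tempting, and the documents do not support them.

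- A reader might infer that the cortisol effect will be biased through every listed covariate. Only breastfeeding has a causal path in the text, and that path runs through PTSD. For cosleeping and menstrual cycle only the timing, not an effect of the intervention, can be established. Some medication may precede randomisation.
- A reader might divide 0.03 to 0.10 SD by d=0.30 and report a loss of 10% to 33% of the effect. The inputs are assumed, and d=0.30 belongs to the primary outcome; for stress reactivity the protocol says only that d is below 0.30.
- A reader might infer that no other cortisol comparison will be reported. The article states none, but it does not exclude one, and it separately plans group differences at different time points for maternal and infant outcomes.

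**Conclusion.** The concern holds as a conditional one. As written, the rule adjusts the between-group cortisol comparison for at least one variable that arises after randomisation and that, by the protocol's own reasoning, the intervention could change. Following it can bias the estimated total effect on a secondary outcome. One possible mediator named in the protocol is enough to make the rule unsuitable for the main comparison.

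Neither the size nor the direction of the bias can be derived from the documents. It is zero if the intervention does not change the covariate. It reaches about 0.03 to 0.10 SD for one mediator only under the assumed 10 to 20 point difference and 0.3 to 0.5 SD association. Smaller arm differences give less; an unmeasured common cause can give more. The primary PTSD analysis does not depend on this rule.

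**What to change.** State that the main between-group comparison for each cortisol outcome is adjusted for centre and variables fixed before randomisation only. Report the model that adds breastfeeding, cosleeping, menstrual cycle and post-randomisation medication as a labelled sensitivity analysis. Say which medication data precede randomisation, since those may stay in the main model. If the rule was also meant for regressions of association, say so separately.

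The cost is a change of wording and one extra model per cortisol outcome, with no new data collection. Intervals in the main analysis may be somewhat wider if the dropped factors explain much of the cortisol variance.
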